## Methods

### Study design

Our trial is a prospective, randomized, single-center, open-label, parallel, 3-arm, non-inferiority trial, the objective of which is to evaluate pain relief and the quality of recovery in laparoscopic renal surgery using TMQLB compared with TPVB. The overall trial scheme is illustrated in Fig. 1 (see Additional file 1 for the SPIRIT Checklist). Institutional research ethics board approval was obtained from Peking Union Medical College Hospital (PUMCH). The trial will be conducted at PUMCH in accordance with the International Conference on Harmonisation (ICH) guideline for Good Clinical Practice (GCP). Full written informed consent will be obtained from each participant by a qualified member of the research team before the intervention. This trial was registered with the US National Institutes of Health Clinical Trials registry (NCT03414281). Participants will be randomized into three groups receiving TMQLB (two dosing groups) or TPVB for postoperative pain control.

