### Interventions

Intravenous access and standard ASA monitoring will be established after patients arrive at the preoperative holding area. Premedication with 1–2 mg midazolam will be considered depending on the patient’s condition. All patients will receive ultrasound-guided block administered by the same experienced attending anesthesiologist. After the block, the anesthesia induction regimen will be as follows: propofol (2 mg/kg body weight), fentanyl (1 μg/kg body weight), and rocuronium (0.9 mg/kg body weight). Patients will be intubated endotracheally. During the surgery, sevoflurane and a mixture of O_2_/N_2_O will be used for maintenance to keep the bispectral index (BIS) within the range of 40–60. Fentanyl will be administered as needed to control the heart rate and blood pressure to within ± 20% of the baseline values.

#### TMQLB experimental group 1

For participants in the TMQLB group 1, the QLB will be performed using the transmuscular approach. The patient is placed in the lateral position. The patient is scanned using the curved (C1–5) probe of the Philip CX50 Ultrasound Scanner is used and is located vertical to the iliac crest at the posterior axillary line to find the Shamrock sign. The 22-G needle is then inserted in plane and directed to the QL muscle. After the proper position of the needle tip between the psoas major muscle and the QL muscle is confirmed, ropivacaine 0.5% at 0. 4 ml/kg body weight with adrenaline at a ratio of 1:200,000 is injected into the interfascial plane. The effective block is confirmed by the sign of local anesthetic spreading around the QL muscle and the loss of sensory function in the area. If there is no block of sensory function after 45–60 min, then it is defined as an unsuccessful block. All interventions will be performed by the same experienced attending anesthesiologist.

#### TMQLB experimental group 2

The intervention in TMQLB group 2 conforms to that used in TMQLB group 1 except that the dose of ropivacaine is 0. 6 ml/kg body weight.

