#### TPVB control group

In the TPVB group, the patient is placed in the lateral position, the spinous processes of vertebra T10 are identified and marks are made 2 cm lateral to the spinous processes. The linear (L12–3) probe of the Philips CX50 is placed transversely at the mark to identify the paravertebral space. Then a 22-G needle is inserted in-plane in a lateral to medial direction and advanced until the tip reaches the paravertebral space surrounded by the parietal pleura and the superior costotransverse ligament. Then, ropivacaine 0.5% at 0.4 ml/kg body weight with adrenaline at a ratio of 1:200,000 is injected into the paravertebral space of vertebra T10. The block is confirmed as correct by the sign of the parietal pleura being pressed down by the local anesthetic. A successful block is defined as loss of sensory function in the area.

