#### Secondary outcomes

Secondary outcomes are as follows:Mean VAS score in the first postoperative 24 h between TMQLB group 2 and the TPVB group. In theory, the dose of local anesthetic in TMQLB group 1 is lower than that in TMQLB group 2, hence, if group 1 satisfies the non-inferiority hypothesis, the mean VAS score in group 2 should also be non-inferior to that in the TPVB group. If not, the results of the comparison between TMQLB group 2 and the control will be hypothesis-generating.Cumulative morphine consumption, which will be registered at 0, 2, 4, 8, 12, 24, 48 and at 72 h and 7 days after surgery, and will be calculated as the sum of the values.Long-term pain control, which will be evaluated by VAS at 48 and 72 h and at 7 days after surgery.Dermatomal distribution of sensory loss, which will be evaluated at 10, 20, 30 and 40 min after the intervention by pinprick test using Von Frey filaments.Nausea score, which will be recorded at 0, 2, 4, 8, 12, 24 and 48 h after surgery.Pruritus score, which will be recorded at 0, 2, 4, 8, 12, 24 and 48 h after surgery.Ambulation timeTime of recovery of bowel movement (defined as the time to first flatus).Quality of recovery evaluated by the self-assessment quality of recovery (QoR) scale at 3 days and 5 days after surgery. The QoR is a 15-item questionnaire, scored on a scale of 0–10 pertaining to the patient’s comfort, support system, pain, wellbeing and ability to carry out daily activities, where 0 indicates none of the time and 10 indicates all of the time [11].Length of postoperative of hospital stay.Patient satisfaction with anesthesia evaluated using the Chinese version of the Bauer questionnaire at 48 h after surgery [12].

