### Sample size calculation

The primary outcome of this non-inferiority trial is the mean VAS score in the first postoperative 24 h in TMQLB group 1 (ropavacaine 0.4 ml/kg body weight) and the TPVB group. Hence, we used the sample size estimation with the non-inferiority test for the difference between two means using PASS 15 software. A higher VAS score in clinical practice indicates that the patients suffer worse pain. No non-parametric adjustment was used in the sample size calculation. We used statistical power of 90% and two-sided α of 0.05. Based on our pilot study, the VAS scores in TMQLB group 1 and the TPVB group were 3.35 and 3.08, respectively, and the standard deviation (SD) of the mean VAS score was 0.5. The non-inferiority margin was set as 0.616 (20% of the VAS score in the TPVB group). The target sample size for each group is at least 36 participants. Considering a potential dropout rate of 10% in the postoperative data collection, we plan to include 40 patients in each group.

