### Data analysis

We will first describe the baseline characteristics of the participants and compare the group difference using the standardized difference; a standardized difference smaller than 0.2 will be considered acceptable deviation between groups [19]. The distribution of the variables will be checked by visual inspection of the histogram. Normally and non-normally distributed variables will be described by the mean ± SD or median (interquartile range (IQR)).

In all data analyses, we will first compare TMQLB group 1 with the TPVB group. If the result is negative, then we will compare data for TMQLB group 2 with the TPVB group to explore whether increasing the amount of local anesthetic would improve the outcome of TMQLB.

Since the primary outcome of the mean VAS score in the first postoperative 24 h is generally normally distributed as reported by Dai et al. [13], the result will be expressed as mean ± SD. Student’s *t* test will be used to compare the difference in the mean postoperative VAS score between TMQLB group 1 and the TPVB group, and the mean difference with corresponding one-sided 95% CI will be calculated. If the upper bound of the one-sided 95% CI is smaller than 0.616, we will reject the null hypothesis in the non-inferiority test and conclude that the mean VAS score in the first postoperative 24 h in TMQLB group 1 is non-inferior to that in the TPVB group.

For the secondary outcomes, the mean difference in the VAS score between TMQLB group 2 and TPVB group, cumulative morphine consumption and long-term VAS scores will be analyzed using the non-inferiority test, while other variables will be analyzed using the superiority test. For continuous data, Student’s *t* test will be used for parametric data analysis and the Mann-Whitney test will be used for non-parametric data analysis, including data on morphine consumption which are often reported as highly skewed. The time-to-event data including time of bowel movement recovery, ambulation time and length of hospital stay will be analyzed by Kaplan-Meier estimates to obtain the survival curves and then the log-rank test will be used to compare curves between groups.

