In the case of data missing or dropouts, data analysis will be performed according to the intention-to-treat principle. The results of this trial will be reported according to the Consolidated Standards of Reporting Trials (CONSORT) statement [17]. All data analysis will be performed using SPSS software (version 22; SPSS Inc., Chicago, IL, USA).

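### The non-inferiority claim is tied to intention-to-treat as the only named analysis principle, and intention-to-treat is also given as the handling of missing data, which it cannot be

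*Protocol article*

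**What the plan says.** The article describes the design as follows: "Our trial is a prospective, randomized, single-center, open-label, parallel, 3-arm, non-inferiority trial". The decision rule in Data analysis is a single comparison of TMQLB group 1 with TPVB: "If the upper bound of the one-sided 95% CI is smaller than 0.616, we will reject the null hypothesis". The same section closes its account of incomplete data with one sentence: "In the case of data missing or dropouts, data analysis will be performed according to the intention-to-treat principle". No other analysis principle is named.

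Three further places bear on block success:

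- **TMQLB experimental group 1** confirms the block by a spread sign and a sensory sign, and adds a timed failure rule: "If there is no block of sensory function after 45–60 min, then it is defined as an unsuccessful block".
- **TPVB control group** uses a pleural ultrasound sign, and then: "A successful block is defined as loss of sensory function in the area". It gives no time limit and no failure rule.
- **Secondary outcomes** schedules sensory testing of the dermatomes, "which will be evaluated at 10, 20, 30 and 40 min after the intervention by pinprick test using Von Frey filaments".

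Trial safety adds that the procedure is halted if an adverse event occurs during it, so an incomplete block is foreseen. The article does not say how a failed or halted block is analysed.

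**The concern.** There are two problems.

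**Robustness.** In a superiority trial, including patients who did not receive an effective version of their allocated treatment usually makes the claim harder to reach. In a non-inferiority trial it can make the claim easier, because such patients may have similar pain whichever block was intended. A positive result from intention-to-treat alone then cannot be told apart from dilution. The usual safeguard is a per-protocol analysis that must reach the same conclusion.

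**Missing data.** The primary outcome is the mean of VAS scores at six times (0, 2, 4, 8, 12 and 24 h). A patient with a gap has no defined value, and naming intention-to-treat does not create one. The sample size section expects 10% loss in postoperative data collection, so the question will arise.

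The stakes are practical. The Discussion says that a positive result could lead to TMQLB being recommended as an alternative to TPVB.

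**Working it through.** **Inputs from the article (Sample size calculation, Data analysis).** Pilot means 3.35 (TMQLB group 1) and 3.08 (TPVB), so the expected difference is 0.27; SD 0.5; margin 0.616; power 90%; 36 per group, 40 after 10% dropout.

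**Step 1: reproduce the plan's figure.** n = 2·SD²·(z₁₋α + z_power)² / (margin − difference)².

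- One-sided alpha 0.05: 2 × 0.25 × (1.645 + 1.282)² / 0.346² = 35.8, so 36. This matches.
- One-sided alpha 0.025: 2 × 0.25 × (1.960 + 1.282)² / 0.346² = 43.9, so 44. This does not match.
- 36 / 0.9 = 40. This matches.

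The stated n therefore follows the one-sided 95% bound in Data analysis and not the literal wording "We used statistical power of 90% and two-sided α of 0.05". That mismatch is a separate matter; one-sided 0.05 is used below.

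**Step 2: dilution in its simplest form.** Assume a fraction f of blocks fails in each arm, failed blocks have the same mean VAS in both arms, and the true difference among successful blocks equals the margin. The difference over all patients is 0.616 × (1 − f):

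- f = 5%: 0.585
- f = 10%: 0.554
- f = 20%: 0.493

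SE = 0.5 × √(2/36) = 0.1179. With no extra variance from failures, P(claim) = Φ((0.616 − diluted difference)/0.1179 − 1.645), which gives 8%, 13% and 27%.

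**Step 3: let failures add variance.** If failed blocks have a different mean, each arm's variance becomes 0.25 + f(1 − f)(μ_success − μ_fail)². Example with f = 10% and an assumed failed-block mean of 4.5:

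- TMQLB variance: 0.25 + 0.09 × 0.804² = 0.308
- TPVB variance: 0.25 + 0.09 × 1.42² = 0.432
- SE: √((0.308 + 0.432)/36) = 0.143
- P(claim): Φ(0.062/0.143 − 1.645) ≈ 11%

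Simulation of the t test (100,000 runs, 36 per arm, one-sided 0.05), with failed-block means of 3.7, 4.5 and 5.5:

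| Failures TMQLB / TPVB | Mean 3.7 | Mean 4.5 | Mean 5.5 |
|---|---|---|---|
| 5% / 5% | 8.0% | 7.4% | 6.3% |
| 10% / 10% | 12.4% | 10.5% | 8.4% |
| 20% / 20% | 25.2% | 18.2% | 12.1% |
| 0% / 10% | 12.6% | 25.5% | 39.2% |
| 10% / 0% | 5.0% | 1.2% | 0.3% |

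The last two rows show that the direction depends on where the failures occur.

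**Step 4: set the block-success passages side by side.** Both techniques share a sensory-loss criterion. They differ in the ultrasound sign and in the time limit, which is 45–60 min for TMQLB and absent for TPVB. The scheduled dermatomal tests end at 40 min, before the TMQLB window opens. An intention-to-treat comparison uses none of these definitions. Any analysis that classifies blocks as successful or failed does.

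**The case against.** The strongest reply is that an article condenses a fuller protocol, and that a statistical analysis plan not shown may define a per-protocol set and an imputation method. That is fair. The article does not rule out a second analysis, and its silence on one is not an error in itself. What stands is the text it does fix: one decision rule, one named principle, and a sentence that assigns missing data to a principle that does not handle them. A later plan would still have to correct that sentence.

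A reader might infer more than the documents support:

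- **That failed blocks are stated to be included.** They are not. The sentence covers missing data and dropouts; inclusion follows only from a strict reading of intention-to-treat.
- **That intention-to-treat necessarily favours non-inferiority here.** It does not. Failures confined to TMQLB leave the error rate at 5% or lower it.
- **That the uneven success definitions bias the primary comparison.** They cannot, because that comparison does not use them.
- **That the test schedule flatly contradicts the failure rule.** The 10–40 min tests belong to a secondary outcome, and nothing says they are the only sensory checks. The accurate statement is that the time limit is given for one technique only and no scheduled test falls within it.
- **That 8%, 13% and 27% are the likely error rates.** Those figures assume that failures add no variance, and they lie at or above the top of the simulated ranges.
- **That the 10% inflation contradicts intention-to-treat.** It is an ordinary allowance for lost data.

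A further objection is that failure may be a consequence of the technique, so that excluding failed blocks can be the lenient choice. Assume success-only means of 3.48 and 3.08, with 15% TMQLB failures at VAS 5 and none in TPVB. The TMQLB mean over all patients is 0.85 × 3.48 + 0.15 × 5 = 3.708. The difference is then 0.628, above the margin, while the success-only difference is 0.40, below it. This objection stands in full and shapes the fix.

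**Conclusion.** The point holds in a limited form. Intention-to-treat is the only principle named for the non-inferiority claim, and alone it cannot show that a positive result is robust. As a statement of how missing data are handled, it is wrong.

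The size is illustrative. With equal failures of 5%, 10% and 20% the false non-inferiority rate is about 6–8%, 8–12% and 12–25%, against a nominal 5%. With 10% failures in TPVB alone it is 13–39%; with 10% in TMQLB alone it is 5% down to 0.3%. These figures rest on assumed failure rates, on assumed failed-block means of 3.7 to 5.5 common to both arms, and on a true difference exactly at the margin. None of these comes from the documents. False here refers to the difference among successful blocks; a reader interested only in the effect of the allocated policy would judge it differently.

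The uneven timing of block success is real, but it matters only for analyses that classify blocks by success.

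**What to change.** 1. Keep intention-to-treat, defined as all randomised patients analysed as allocated. Add a pre-specified per-protocol analysis: allocated block given, no major deviation, VAS to 24 h available. Claim non-inferiority only if both upper bounds are below 0.616.
2. Report the exclusion of failed blocks as a sensitivity analysis and not as the per-protocol definition, because it selects on a post-randomisation outcome that the technique may itself cause.
3. Replace the missing-data sentence with a method: a mixed model for the repeated VAS values or multiple imputation of them. Add a sensitivity analysis that penalises imputed TMQLB values, for example by adding the margin of 0.616.
4. Reconcile the TMQLB, TPVB and Secondary outcomes passages so that block success is judged by the same sensory criterion at the same scheduled time in all three arms. Which criterion and time to use is for the investigators to decide.

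**Cost.** Changed wording and one more analysis. Joint power cannot exceed that of the smaller set. At the planned difference of 0.27, SD 0.5 and one-sided alpha 0.05, t-based power is 92.3% with 40 per arm and 89.7% with 36, and somewhat lower if deviations remove more patients.

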## Discussion

Although QLB is gaining popularity as analgesia in abdominal surgery, there has been limited clinical study of its clinical efficacy compared with other truncal block techniques. Most of the current studies concentrate on the comparison of QLB with other abdominal blocks, especially the transversus abdominis plane (TAP) block, because QLB was originally proposed as a different form of TAP [4, 5, 15, 16]. Also, the analgesic mechanism of TMQLB is still controversial. The anatomical work performed by Børglum et al. [9] reveals that in TMQLB the injectate spreads cephalad to the thoracic paravertebral space. This convincing study prompted us to speculate that TMQLB may have a similar analgesic profile to TPVB, which is essentially a thoracic truncal block, and this inspired us to conduct a trial to compare these two block techniques and further validate the theory from a clinical aspect.

The expected results will provide clinical evidence to verify the analgesic mechanism of TMQLB put forward by Børglum and promote its application in intraperitoneal and retroperitoneal surgery. Furthermore, if the efficiency of TMQLB is equal to that of TPVB, TMQLB could replace TPVB in abdominal surgery because it is relatively safe and convenient to perform, while TPVB implicates a possibility of pneumothorax, dural puncture and hematoma in the thoracic paravertebral space [10, 14].

As the mechanism of the injectate of TMQLB reaching the paravertebral space is primarily by spreading via the pathway posterior to the arcuate ligaments, it could be assumed that the amount of the injectate will consequently determine the extent to which the thoracic nerves are blocked. Henceforth, we designed three intervention groups with two dosing groups for TMQLB to explore whether the amount of injectate would improve the coverage and analgesic effect. This may also provide a clue to the appropriate dosage for anesthetics in TMQLB.

To the best of our knowledge, the present study will be the first to compare TMQLB and TPVB for the purpose of assessing the clinical effectiveness and safety of TMQLB in laparoscopic renal surgery. The proposed trial is a prospective, randomized and blinded-analysis trial with rigorous methodology to avoid potential risk of bias. Since the nature of the intervention makes it impossible for the participant and the investigator performing the block to be blinded, the outcome assessor and statistician will be blinded to the allocation to keep the data analysis unbiased. In addition, the strict process of randomization and allocation of each participant could reduce the risk of selection bias.

If our trial yields positive results, there is potential that TMQLB could be recommended as an alternative nerve block for postoperative analgesia in abdominal surgery, to circumvent the need for TPVB.

### Trial status

This trial was initiated in January 2019. At the time of manuscript submission, the recruitment is ongoing.

## Abbreviations

ASA: American Society of Anesthesiologists
ASRA: American Society of Regional Anesthesia and Pain Medicine
BMI: Body mass index
CRF: Case report form
EDC: Electronic data capture
GCP: Good Clinical Practice
ICH: International Conference on Harmonisation
IPCA: Intravenous patient-controlled analgesia
IQR: Interquartile range
PACU: Postanesthesia care unit
PUMCH: Peking Union Medical College Hospital
QL: Quadratus lumborum
QLB: Quadratus lumborum block
QoR: Quality of recovery
RCT: Randomized clinical trial
SD: Standard deviation
TMQLB: Transmuscular quadratus lumborum block
TPVB: Thoracic paravertebral block
VAS: Visual analogue scale
